## Methods

The study was retrospectively registered on the 1st of September, 2020 in Clinicaltrials.gov (NCT04535258). The reporting of this study is in accordance with the Standard Protocol Items: Recommendations for Interventional Trials (SPIRIT) guidelines [45, 46].

### Study design

The study is a pragmatic, stepped wedge cluster randomized controlled trial [46].

After implementation of the BLEND-A protocol in the participating treatment institutions, we expect that 25–40% of the consecutively enrolled patients will be offered blended treatment and accept to receive it. The decision of whether a patient will receive blended treatment will be made by the therapist and patient together during the first treatment session, taking into consideration the participant’s education, literacy, and computer skills.

Patients not receiving blended treatment are expected to continue receiving face-to-face treatment only. Up to 40 % of the patients are assumed to make use of the possibility of blended treatment. Thus, randomization to BLEND-A treatment and face-to-face treatment is not considered possible at the individual level due to the element of shared decision making in the blended care protocol. Instead, we will use a stepped wedge cluster randomized design [47] and randomize the treatment institutions to implement a new routine in which BLEND-A is offered to patients as a possible alternative to face-to-face treatment.

The BLEND-A study design is, thus, a pragmatic, stepped wedge cluster randomized controlled trial of a blended treatment alcohol intervention incorporating evaluations of the clinical effectiveness of the intervention, its economic impact, its perspectives for sustainable implementation in routine practice, and its impact on patient wellbeing and functioning.

### Study procedure and randomization

All 61 publicly funded Danish treatment institutions were invited to participate in the effectiveness and implementation study. A total of 18 treatment institutions are included in the study. The included institutions are scattered all over the country, and the catchment areas cover approximately 30% of the Danish population.

The stepped wedge cluster randomized design includes an initial period in which no clusters are exposed to the intervention. Subsequently, at regular intervals of 3 months, one cluster or a group of clusters are randomized to cross from the control group to the intervention group. In the present study, the participating institutions were randomized into 1) first-movers, 2) second-movers, 3) third-movers, and 4) fourth-movers (see Fig. 1.).

**Fig. 1 Fig1:**
[figure not shown]
Enrollment of groups of participating institutions (clusters) to the BLEND-A intervantion

First-movers will implement BLEND-A first, and second-movers will implement BLEND-A 3 months later. Third-movers and fourth-movers will implement BLEND-A after another 3 and 6 months. Hence, the patients being treated at an institution before implementation will serve as control groups until the institution implements BLEND-A.

The randomization of the institutions into the four waves of movers occurred by 1) attributing the participating institutions a random number, and 2) elaborating six different models for implementing the institutions (numbers) into the different waves of the study. The randomization procedure was designed by the research group. The models were placed in separate envelopes and then an independent staff member (a statistician not part of the research group) selected one, which was subsequently applied to designate the institutions into first-, second-, third- or fourth movers.

All individuals seeking treatment for AUD at the participating treatment institutions during the study period will be invited to participate as a routine part of the intake procedure at the institutions.

### Interventions

#### Treatment as usual

In Denmark, the public treatment for AUD is delivered by the local governments in the municipalities, and the treatment is free for patients. No referral is needed for treatment [48]. By law, the local governments can choose to establish their own treatment institutions or ask an organization to deliver the treatment. All the treatment institutions in the present study are operated by the municipalities. At the clinics, patients´ psychological treatment consists of MI and CBT [48–50]. Pharmacological treatment may also be provided, administered by the clinic or in collaboration with the patients’ General Practitioners. The psychosocial interventions are typically delivered during individual weekly or bi-weekly sessions alone or in combination with group therapy, and the duration typically varies from 4 to 6 months. The staff typically includes nurses, social workers, therapists, psychologists, and medical doctors, all of whom have received post-graduate training in the treatment of addictions [48].

#### BLEND-A treatment

As preparation for the study, the blended treatment approach platform from the Jellinek clinics was translated into Danish by the study group in the spring of 2017. Therapists and patients from three alcohol treatment institutions (Svendborg, Haderslev, and Kolding) in Denmark were involved in translating and adapting the treatment protocol. The internet-based modules as well as the protocol for the face-to-face sessions in the treatment pathway were translated, adjusted to Danish culture, and adapted accordingly.

The fully translated treatment protocol, internet-based modules, and procedures for access and data flow, were pilot tested in 2018 to explore usability, acceptability, technical and organizational integration, adaption to Danish context, and preliminary effectiveness of the intervention. Two therapists from each of the participating alcohol treatment institutions (Svendborg, Haderslev, and Kolding) implemented the pilot BLEND-A in a total of 22 individual treatment pathways. The pilot test ran for 6 months. After the pilot-study, focus group interviews were conducted with patients and therapists [44]. The treatment protocol was adjusted during the testing process.

The Blend-A platform is hosted by the Dutch company, Minddistrict, and it is accessible via any given web-browser. The online sessions follow the course of the ordinary treatment offer; a fixed structure starting with therapy information, followed by multiple exercises and homework assignments, training in optional skills adjusted to the patients’ individual needs, and relapse prevention. The platform offers four modules. The first module, Welcome and preparation, lasts for approximately 30 min. The second module comprises nine submodules addressing different aspects of treatment: a) Motivation, b) Treatment goals, c) Risk situations, d) Functional analysis, e) Relapse prevention strategies, f) Coping with craving, g) Restructuring of thoughts, h) Communication training focusing on saying no to alcohol, and i) Evaluation of the treatment course (each lasting approximately 30 min). The third module comprises seven submodules that are optional: a) Social skills - small talk, b) Social skills – tackling criticism, c) Social skills – giving criticism, d) Mood management, e) Stress management, f) Problem solving strategies, and g) Tackling relapse (each lasting approximately 30 min). The fourth module includes six submodules focusing on aftercare, primarily monitoring alcohol use and quality of life (each lasting approximately 15 min).

The therapist can gradually add online sessions to the patient’s individual platform. The online sessions contain text and videos with information as well as assignments. Patients receive online feedback about assignments from their therapist. The platform allows the sharing of information and homework assignments with significant others. If a patient stops being active in treatment, the therapist will contact him/her by email, phone, or video, or if needed, invite him/her to resume face-to-face treatment. Thus, the Internet-based modules and face-to-face treatment can be combined in numerous ways.

It is estimated that the active blended treatment course will last for 3 months. Thereafter, the patients can use the platform for relapse prevention for up to 6 months. Upon completion of treatment, the patients will continue to have access to the online treatment platform so they can re-read information and look up exercises.

#### Training of therapists

MI and CBT are the most widely used treatment modalities for AUD in Denmark. Most Danish alcohol therapists have participated in the Basic training for Alcohol Therapists (lasting 16 days), offered by the National Health and Medicine Authority. The training offers a solid introduction to MI and CBT and thereby to the treatment content of the blended protocol. In addition, most treatment institutions offer regular ongoing training in MI and CBT to their therapists.

The BLEND-A Study includes a one-day training session in the BLEND-A protocol for all therapists involved. During the training, they will learn how to navigate the online platform and practice with the different modules. Initially, the training will be provided by experts in the field of internet-based treatment (from the Centre for Telepsychiatry). All therapists from the participating institutions will be offered the training before the implementation phase begins at their institution, and they will receive a manual instructing how to use the platform.

They will thereafter obtain access to the web-based part of BLEND-A via Sundhed.dk and will be encouraged to invite future patients to blended treatment.

#### Intervention fidelity and access to supervision

A key therapist from each of the participating treatment institutions will receive additional training in the protocol and function as a local supervisor. Further, a therapist from each institution will be offered the opportunity to participate in a full day follow-up network meeting every month (10 days per year) during the study period, where the project group will also be represented. In this meeting, practical questions and considerations about how to make the intervention work can be sorted out in order to secure intervention fidelity. In addition, a help desk operated by the Centre for Telepsychiatry will be made available to the key therapists. The use of the internet-based modules will be registered and monitored throughout the study period.

### Data collection

All patients from each of the participating treatment institutions will be followed up in the National Register of Alcohol Treatment (NAB). In accordance with Danish Law, this register contains data on all patients receiving publicly funded treatment for AUD. The register provides data on sociodemographic characteristics, compliance, and alcohol related variables (see Table 1).

**Table 1 Tab1:** Data collected during the BLEND-A study

Domain	Measure/source	Content	Reference	Time-point
Descriptive variables				
Sociodemographics and treatment data	National Alcohol Treatment Register (NAB)	Gender, age, education, etc. and treatment duration and intensity as well as prior treatment.	[51, 52]	Treatment entry and treatment completion
Primary outcomes				
Compliance	National Alcohol Treatment Register (NAB)	Treatment retention and type of treatment conclusion (i.e. dropout or completion).		Registered on continuous basis in the national register
Secondary outcomes				
Alcohol consumption	Alcohol Use Disorders Identification Test (AUDIT)	Items from the AUDIT: Quantitiy/frequency measure of alcohol consumption.	[53]	Treatment entry and 6-month follow-up post treatment
AUD severity	Alcohol Use Disorders Identification Test (AUDIT)	AUDIT asesses AUD, alcohol consumption, drinking behaviors, and alcohol-related problems	[53]	Treatment entry and 6-month follow-up post treatment
	Alcohol Dependence Scale (ADS):	ADS measure the severity of alcohol dependence symptoms.	[54, 55]	Treatment entry and 6-month follow-up post treatment
	Short Inventory of Problems-2 Revision (SIP-2R)	SIP-2R evaluates alcohol-related problems.	[56]	Treatment entry and 6-month follow-up treatment
	National Alcohol Treatment Register/ Addiction severity Index (ASI)	ASI assesses multidimesional addiction severity related to various domains: alcohol and drug use, physical and mental health, employment, legal problems and social functioning.	[51, 52]	Treatment entry and treatment conclusion
Quality of life	European Quality of life - 5 Dimensions (EQ5D)	EQ5D evaluates quality of life on five dimensions: mobility, self-care, usual activities, pain/discomfort, and anxiety/depression.	[57, 58]	Treatment entry and 6-month follow-up post treatment.
Usability of blended treatment	System Usability Scale (SUS)	SUS evaluates the usability of the web-based treatment system.	[59]	6-month follow-up post treatment.

Institutional level data will cover 1 year before treatment start until the end of the study period for all consecutive patients at the participating treatment institutions.

In addition to the register data, all patients seeking treatment at the participating treatment institutions during the study period will be asked to complete a questionnaire at treatment start and after treatment completion 6 months later. The questionnaire will consist of questions on the patients’ contact information, alcohol consumption, consequences of drinking, quality of life and usability of the internet-based platform (see Table 1).

The questionnaire will be administered via tablets at the treatment institutions or by secure mail or telephone interviews conducted by blinded research assistants. If a patient stops treatment before the 6 months follow up, the questionnaire will be emailed to him/her via a safe link or administered over the phone by a researcher. The questionnaire-based data will be collected from patients in both the intervention and the control groups. Data will be collected using REDCap™ (Research Electronic Data Capture), which is a secure web application for building and managing online data entry systems [60], and stored in OPEN, Open Patient data Explorative Network, Odense University Hospital, Odense. Data on use of the BLEND-A modules will be obtained from the platform.

Randomly chosen patients and therapists will be asked to participate in additional qualitative interviews, conducted either individually or in focus groups to investigate how participation in blended care is experienced by the users. An interview guide will be developed, which will allow the patients and therapists to describe both the challenges and opportunities associated with the blended treatment approach [61].

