**Methods:**

The study design is a pragmatic, stepped-wedge cluster randomized controlled trial. The included outpatient institutions (planned number of patients: *n* = 1800) will be randomized in clusters to implement either blended AUD treatment or face-to-face treatment only, i.e. treatment as usual (TAU). Both treatment approaches consist of motivational interviewing and cognitive behavioral therapy. Data on sociodemographics, treatment (e.g. intensity, duration), type of treatment conclusion (compliance vs. dropout), alcohol consumption, addiction severity, consequences of drinking, and quality of life, will be collected at treatment entry, at treatment conclusion, and 6 months after treatment conclusion. The primary outcome is compliance at treatment conclusion, and the secondary outcomes include alcohol consumption and quality of life at six-months follow-up. Data will be analyzed with an Intention-to-treat approach by means of generalized linear mixed models with a random effect for cluster and fixed effect for each step. Also, analyses evaluating cost-effectiveness will be conducted.

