#### Power calculations and number of participants needed in the study

In 2014, 31% of all patients seeking treatment at a publicly funded alcohol treatment institution completed the treatment pathway as planned [12, 66]. We hypothesize that implementing BLEND-A will lead to a 10-percentage point higher level of compliance compared to TAU, i.e. increasing the total number of patients who complete the treatment course at the treatment institution according to the NAB register.

We wish to be able to identify a 10-percentage point increase in overall treatment completion (from 31% now with treatment as usual to 41% with BLEND-A) with 80% power and a two-sided significance level of 5%. In order to secure the randomization process, we aim to involve at least two major institutions (enrolling more than 200 new patients per year, typically 300–600 patients), and additionally 6 or more minor treatment institutions (typically enrolling 60–80 new patients per year [66]). The power calculation, based on Hemming et al.’s recommendations for stepped wedge cluster randomized trials [47, 67], estimates that a total of 1800 individuals, enrolled in treatment at such 8 treatment centers and enrolled in four steps (the first two steps were 6 months apart, the others steps were 4.5 months apart) during a period of 20 months, will be sufficient to detect a 10 percentage point improvement with at least 80% power. Register data stemming from the year prior to the start of enrollment will be regarded as the first step. The figure below shows the power as a function of the improvement for various situations of intra-center-correlations, and the power is exceeded when the effect is a 10-percentage point improvement from 31 to 41% as specified.

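### The register-based ASI outcome is timed by treatment conclusion, an event the intervention is meant to change, and its capture in patients who drop out is not secured

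*Protocol article*

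**What the plan says.** In the protocol article, Table 1 (Data collection) places ASI among the secondary outcomes, under AUD severity, with the national alcohol treatment register as its source. Its time-points are "Treatment entry and treatment conclusion". The other severity instruments, AUDIT, ADS and SIP-2R, are listed at entry and at a 6-month follow-up.

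The same table describes the primary outcome, compliance, as "Treatment retention and type of treatment conclusion (i.e. dropout or completion". The abstract likewise speaks of "type of treatment conclusion (compliance vs. dropout". Conclusion is thus the end of any treatment episode, whether planned or not. On coverage, Data collection states that "this register contains data on all patients receiving publicly funded treatment for AUD".

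The power section reports that in 2014 "31% of all patients seeking treatment at a publicly funded alcohol treatment institution completed the treatment pathway as planned", and it plans for an increase "from 31% now with treatment as usual to 41% with BLEND-A". For patients who leave early, Data collection says: "If a patient stops treatment before the 6 months follow up, the questionnaire will be emailed to him/her via a safe link", or that it will be given by phone. No similar step is described for the register ASI. The Data analysis section states an intention-to-treat approach.

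**The concern.** A secondary outcome used to compare conditions should be measured at a time that the intervention does not set. Here the second ASI is taken when the episode ends, and when and how it ends is the primary outcome.

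This raises two issues. The first is timing: patients who drop out conclude early, completers conclude later, and blended and usual courses have different expected lengths. Severity changes over time after entry, so a between-condition difference in ASI could appear or disappear because of when it was measured. The second is capture: a register entry that an episode ended in dropout does not by itself mean that an ASI was obtained from a patient who no longer attends. If few dropouts have a value, the patients compared are partly selected by the primary outcome. An effectiveness statement on ASI would then be hard to interpret, even when patients are analysed by allocated condition.

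**Working it through.** The plan gives no figure for ASI or its expected completeness, so there is none to reproduce.

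**Inputs from the article**
- Planned completion: 31% under usual treatment, 41% with BLEND-A (power section). Non-completion is therefore 69% and 59%.
- Expected duration: typically 4 to 6 months for usual treatment (Treatment as usual); about 3 months for the active blended course (BLEND-A treatment).
- Expected uptake of blended treatment after implementation: 25 to 40% (Study design).

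**Assumptions, not in the article**
- r, the correlation between latent severity and dropping out: 0.3 to 0.5.
- f, the share of dropouts with an ASI at conclusion: 0 to 1, taken at random among dropouts.
- Blended users would otherwise have had a usual course of typical length, and conclusion falls at the end of the active course.

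**Step 1: timing, even with complete capture.** For a blended user who completes, conclusion comes 4 − 3 = 1 to 6 − 3 = 3 months earlier than under usual treatment. With 25 to 40% uptake, the average shift among completers is 0.25 × 1 = 0.25 to 0.40 × 3 = 1.2 months. Turning early dropouts into completers moves the average the other way. The net direction is therefore not known in advance, but time since entry is not held constant between conditions.

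**Step 2: who would contribute ASI data.** The completers' share of ASI values is p / (p + f(1 − p)), where p is the completion proportion.

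| f | Usual treatment (p = 0.31) | BLEND-A (p = 0.41) |
|---|---|---|
| 0 | 100% | 100% |
| 0.25 | 64% | 74% |
| 0.50 | 47% | 58% |
| 0.75 | 37% | 48% |
| 1 | 31% | 41% |

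Completers are the majority only if f is below 0.31/0.69 = 0.45 under usual treatment, or below 0.41/0.59 = 0.69 under BLEND-A.

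**Step 3: size of a selection artefact with no treatment effect on severity.** Let a normal latent tendency to stay determine completion, and let φ(z) be the normal density at the cut-off. Completers have mean tendency φ(z)/p and dropouts −φ(z)/(1 − p). Among assessed patients the mean is (1 − f)φ(z) / (p + f(1 − p)). Here φ(z) = 0.3528 at p = 0.31 and 0.3887 at p = 0.41. The artefact is r times the difference between conditions.

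With f = 0: 0.3528/0.31 = 1.138 and 0.3887/0.41 = 0.948. The difference is 0.190, which gives 0.06 SD at r = 0.3 and 0.09 SD at r = 0.5.

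| f usual / f BLEND-A | Difference | r = 0.3 | r = 0.5 |
|---|---|---|---|
| 0 / 0 | 0.190 | 0.06 SD | 0.09 SD |
| 0.10 / 0.10 | 0.092 | 0.03 SD | 0.05 SD |
| 0.25 / 0.25 | 0.025 | 0.01 SD | 0.01 SD |
| 0.40 / 0.40 | 0.000 | 0.00 SD | 0.00 SD |
| 0.50 / 0.50 | −0.006 | 0.00 SD | 0.00 SD |
| 0.25 / 0.35 | 0.139 | 0.04 SD | 0.07 SD |
| 0.10 / 0.20 | 0.249 | 0.07 SD | 0.12 SD |
| 0.35 / 0.25 | −0.107 | −0.03 SD | −0.05 SD |

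Positive values count against BLEND-A if more severe patients are likelier to drop out; if they are likelier to stay, every sign reverses. Unequal capture is possible on the text: contacting inactive patients by email, phone or video is described as part of BLEND-A treatment, and the description of usual treatment mentions no such step.

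**Step 4: a yardstick.** An assumed effect of 0.2 SD among blended users becomes 0.2 × 0.25 = 0.05 to 0.2 × 0.40 = 0.08 SD at institution level. The artefact is of that size only if capture in dropouts is close to nil or differs between conditions.

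**The case against.** A reader might infer from the 31% completion figure that ASI is compared mainly in completers, that 59 to 69% of patients will lack it, and that the result is biased against BLEND-A. The article does not support this. Dropout is itself a type of conclusion, the register covers all publicly treated patients, and no completers-only rule appears. How the register obtains ASI items when a patient stops attending is a matter of register procedure that the article does not describe. The absence of a chase-up rule for statutory data does not show that those data are missing.

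The larger figures need almost no capture in dropouts. With equal capture of 25% or more the artefact is about 0.01 SD or less. The direction is also assumed: the article has no severity data on the patients whom BLEND-A would retain. ASI is measured at entry too, and adjusting for it would remove part of any difference due to pre-existing severity. Such handling may sit in an analysis plan that is not shown. Nor do missing values alone make an analysis by allocated condition something other than intention-to-treat. Finally, ASI appears in none of the four hypotheses, and three other severity measures exist.

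All of this stands, and it limits the selection argument to a risk. It does not answer the timing point, because Table 1 itself fixes the assessment at an event that depends on the intervention, and full register capture would not change that.

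**Conclusion.** The point holds in a limited form. As written, the plan compares ASI between conditions at times since entry that depend on condition and on dropout status, and it describes no step that secures ASI in patients who leave early. The timing defect follows from the article's own text. Selection bias depends on the unstated share of dropouts assessed. With an assumed correlation of 0.3 to 0.5, it runs from 0.06–0.09 SD with no capture to about 0.01 SD with 25% capture in both conditions. It reaches 0.04–0.12 SD in the examples where capture is 10 points higher under BLEND-A, and it changes sign in the example where capture is higher under usual treatment. The primary outcome is unaffected and ASI is one of several secondary severity measures, so this is a minor-to-moderate point.

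**What to change.** In Table 1, mark ASI at treatment conclusion as descriptive. If it stays a comparative outcome, report with it, for each condition, the share of patients assessed (completers and dropouts separately) and the time since entry, and draw no effectiveness claim from it. Base the between-condition comparison of AUD severity on AUDIT, ADS and SIP-2R at the 6-month follow-up, which the study already seeks from patients who stop early.

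This substitution removes the timing problem only if that follow-up has one fixed anchor that does not depend on conclusion. The hypotheses count 6 months from treatment intake or start, while the abstract counts from treatment conclusion and Table 1 says post treatment. These statements should be reconciled in the same edit.

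The cost is a change of wording and one fewer comparative secondary measure. No new data are needed.
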